### 2.2. Study Participants

Adult (≥18 years old) male and female individuals with chronic (>1 year) traumatic and non-traumatic SCI, with a complete or incomplete lesion according to the American Spinal Injury Association Impairment Scale (AIS A-D), are invited to participate. Individuals experiencing significant GI complaints, indicated with ‘yes’ at screening and a GIQLI score below 110 at baseline (T1), are included. Exclusion criteria are antibiotic use, major dietary changes within 4 weeks before the study, presence of a diagnosed clinically relevant medical condition (e.g., Crohn’s disease, diagnosed eating or GI disorders), intake of significant concomitant medication (e.g., immunomodulating therapy, mesalazines), and pregnancy. No concurrent participation in other clinical trials investigating or potentially affecting GI health is allowed. Non-adherence to the supplementation, defined by missing >25% of supplement doses, can lead to exclusion from the trial at the investigator’s discretion.

Potential participants are recruited by distributing the study information and a flyer within the networks of the Swiss Paraplegic Association, the Swiss Paraplegic Centre, and the Swiss Paraplegic Research. In the case of a low recruitment rate, study information will also be spread through community platforms, both online and in magazines (e.g., Paracontact). Interested participants are contacted by phone or in person to perform the screening, where eligibility criteria are assessed, and the participant is informed about the study and what procedures it entails. Written participant information and an informed consent form are provided. After at least 24 h of consideration time, informed consent will be obtained from each participant.

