## 2. Materials and Methods

### 2.1. Study Design, Setting, and Sample Size

This is a single-center open-label two-arm randomized controlled crossover superiority trial (RCCT) adhering to CONSORT guidelines [39] with a total duration of 20 weeks (Supplementary Material). The study is conducted at the Swiss Paraplegic Research in Nottwil, Switzerland. It involves two 8-week interventions consisting of daily intake of either a probiotic (Biotics-G, Burgerstein AG, Rapperswil-Jona, Switzerland) or a prebiotic (Oat Bran, Naturaplan, manufactured by Swissmill, Zurich, Switzerland) supplement, separated by a 4-week washout period (Figure 1). Group allocation, which determines the order of supplement intake by the participants, is determined using a permuted block randomization (block size 4). For this, a randomization list was created using the statistical software Stata (Stata. Version 18. College Station, TX, USA: StataCorp, 2024). Due to the nature of the supplements, no allocation concealment or blinding of study personnel or participants is possible. Recruitment for this study started in summer 2025, and data collection will continue for two years; the study is therefore expected to end in summer 2027. The low-risk nature of this study warrants a risk-based approach for study monitoring. The study will be conducted in accordance with the Declaration of Helsinki. The study was approved by the Ethics Committee for Northwest/Central Switzerland (EKNZ, ID: 2025-00238, 24 February 2025, Version 2.0). The study is registered at ClinicalTrials.gov (ID: NCT06870331, 2 April 2025). Written informed consent will be obtained from all participants involved in the study.

The sample size was calculated for the primary outcome (changes in GIQLI) based on the results of a previous pilot study [34], applying a clinically relevant mean difference of 10 points on the GIQLI [40,41,42] and correcting for a larger expected variability in the GIQLI in the current study population. Assuming a significance level of 5% and a power of 85%, a sample size of 50 participants, with 25 participants in each group, was determined.

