## 3. Data Analyses

An intention-to-treat analysis will be conducted to minimize potential bias resulting from disruption to baseline equivalence following randomization, which may occur due to participant withdrawal, non-adherence to the study protocol, or excessive missing data. Participants will be included in analyses only where data are available. Protocol deviations, early withdrawals, and loss to follow-up will be documented and evaluated. Basic univariable statistical analysis techniques will be used to describe the study population as well as the primary and secondary outcomes at the different measurement points. To evaluate the longitudinal variation in the primary outcome and secondary outcomes, we will use multilevel mixed-effects models that appropriately account for the within- and between-individual sources of variance in outcome variation. In these models, participants are treated as random effects, while intervention and period are used as fixed effects. All models will be adjusted for the baseline value of the respective outcome measured before each period. To evaluate potential carryover effects, sequence (AB vs. BA) will be included as a fixed effect, and treatment-by-period interactions will be tested. Furthermore, pre-period baselines will be compared to verify that the gut environment returned to its SCI-baseline during washout, and a carryover term will be incorporated into the model to identify residual effects. If significant carryover is detected, a sensitivity analysis using only period 1 data will be performed to provide an unbiased estimate of the intervention effect. Depending on the findings, subgroup analyses may be performed for personal parameters (e.g., sex, lesion level). For the microbiome analyses, diversity indices will be compared using paired *t*-tests while correcting for multiple testing using the Benjamini–Hochberg method. A significance level of 5% will be applied. Protein concentrations will be reported as absolute abundances in pg/mL. Absolute abundance will be tested with mixed-effects models analogous to the primary analysis. The Benjamini–Hochberg procedure will control the false-discovery rate at 5%. Multi-omics integration will employ sparse partial least-squares regression to relate inflammatory proteins, microbial genera, and clinical outcomes (GIQLI, GITT). Statistical software packages to be used include R (Version 4.5.2), Stata (Version 19.0), and SPSS (Version 31.0), or any newer stable version available at the time of data analysis.

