The study is subject to several limitations. The open-label nature of the study might introduce a potential bias. With the probiotic packaging resembling a medicinal product, versus the prebiotic clearly coming from a grocery store, participants may have different expectations for the efficacy of either supplement, which may bias their responses. This is not preventable, given the need for specific packaging for both supplements. Additionally, as diet and lifestyle are not strictly controlled, microbiome changes may be confounded, which in a real-life setting cannot be avoided. Despite not being controlled, by assessing physical activity and nutrition at each timepoint, big lifestyle changes can be detected and taken into consideration when analyzing the data. Further, at home supplementation makes strict control of adherence impossible; however, by asking participants to return empty packages after the intervention period, a sense of control is added and quantification of adherence is possible.

Another potential limitation of this crossover design is the risk of carryover effects, where the physiological and microbial changes from the first intervention might persist into the second period. Given the neurogenic bowel dysfunction inherent in SCI, transit times are prolonged, which could theoretically extend the influence of interventions. However, this risk is mitigated by the implementation of a 4-week washout period, exceeding the 2-week window typically required for the microbiome to revert to baseline after a dietary perturbation, and by employing a rigorous four-tiered statistical framework to detect sequence and period interactions [57,58,59,60].

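### Unblinded staff may exclude non-adherent randomised participants case by case, and nothing keeps those participants in follow-up for the promised intention-to-treat analysis

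*Protocol article*

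**What the plan says.** Protocol article, section 2.2 (Study Participants), on non-adherence: "defined by missing >25% of supplement doses, can lead to exclusion from the trial", with the decision left to the investigator. The sentence stands beside the eligibility criteria, but supplement doses can only be missed after randomisation, so it is a post-randomisation exclusion.

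Section 2.1 (Study Design, Setting, and Sample Size): "no allocation concealment or blinding of study personnel or participants is possible".

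Section 3 (Data Analyses): "An intention-to-treat analysis will be conducted to minimize potential bias resulting from disruption to baseline equivalence following randomization", with the threats named as disruption "which may occur due to participant withdrawal, non-adherence to the study protocol, or excessive missing data". The next two sentences read "Participants will be included in analyses only where data are available" and "Protocol deviations, early withdrawals, and loss to follow-up will be documented and evaluated".

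Section 2.3 (Intervention) describes one adherence check, the return of packages once each intervention period is over. Section 4 (Strengths and Limitations) relies on the same check: "by asking participants to return empty packages after the intervention period, a sense of control is added and quantification of adherence is possible". Table 1 schedules the GIQLI at T1 to T4.

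No section says that an excluded participant is still assessed at the remaining visits.

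**The concern.** Intention-to-treat protects the comparison only if outcomes are obtained from people whatever their adherence. Here the analysis section names non-adherence as a source of bias to be countered, while the participant section allows trial staff to end participation because of it. Once a participant is out and no longer assessed, the available-data rule has nothing to include, and no later analysis plan can recover scores that were never collected.

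Three features make this more than ordinary dropout. The decision is optional for each person who crosses the threshold. The person deciding knows which supplement was being taken and, because packages come back around the T2 and T4 visits, may also know how the participant has fared. The primary outcome is self-reported, and poor tolerance or no perceived benefit are plausible reasons for missing doses. That last link is an inference; the article does not state it.

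The crossover design adds a further cost: one excluded participant can remove a whole within-person comparison, which is where the design gets its efficiency.

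**Working it through.** **What is lost, by time of exclusion** (visit schedule from Table 1; adherence check from section 2.3)

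Supplements are taken daily for 8 weeks, so a period has 8 × 7 = 56 doses and 25% of these is 0.25 × 56 = 14. Missing 15 or more brings a participant under the rule, assuming it applies per period, which the text does not say.

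| Exclusion occurs | GIQLI already held | GIQLI lost | Consequence |
|---|---|---|---|
| During period 1 | T1 | T2, T3, T4 | May have no post-baseline value |
| After period 1, at package return | T1, T2 | T3, T4 | Outcome on the first supplement kept; no within-person contrast |
| During washout or period 2 | T1, T2, perhaps T3 | T4 | No within-person contrast |
| After period 2, at package return | T1 to T4 | None | No loss, provided collected data are kept |

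The second row is the route the article describes most directly. The first and third need non-adherence to come to light within a period. This is possible, since tolerance is documented throughout (section 2.4), but no within-period adherence check is described.

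**The plan's sample size**

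Inputs from section 2.1: difference 10 GIQLI points, significance level 5%, power 85%, N = 50. No SD, sidedness or dropout allowance is stated, so 50 cannot be reproduced independently. It can only be solved backwards. I assume a two-sided test on the within-person difference with n − 2 degrees of freedom:

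power(n) = P(|T| > t(0.975, n − 2)), where T is noncentral t with noncentrality 10·√n / SD.

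Setting power(50) = 0.85 gives SD of differences = 23.1. The normal approximation gives 10·√50 / (1.960 + 1.036) = 23.6.

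**Illustrative effect on power** (SD held at 23.1; losses are assumed)

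| Lost | n | Noncentrality 10·√n / 23.12 | t(0.975, n − 2) | Power |
|---|---|---|---|---|
| 0 | 50 | 3.06 | 2.011 | 85.0% |
| 3 | 47 | 2.96 | 2.014 | 82.7% |
| 5 | 45 | 2.90 | 2.017 | 80.9% |
| 10 | 40 | 2.74 | 2.024 | 76.0% |

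The normal approximation with SD 23.6 gives 82.8%, 81.1% and 76.4% for the last three rows, so the choice of formula hardly matters. The table treats a lost participant as contributing nothing. A mixed model would still take some information from someone with T2 alone, so these are pessimistic values for each assumed loss.

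**Bias**

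A mixed model fitted to the available data copes with loss that depends only on values it contains, such as an observed T2 score. It gives no such assurance when the loss depends on adherence, tolerance or the investigator's judgement, none of which is in the stated model. The article offers no exclusion rate and no outcome difference between excluded and retained participants, so I give no size for the bias.

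**The case against.** The strongest reply is that the two sections deal with different things. Section 2.2 speaks of leaving the trial and section 3 of the analysis. Exclusion is optional, nothing says collected data are discarded, and deviations and withdrawals are to be documented and evaluated. Analysis sets and follow-up after withdrawal are often set out in a fuller protocol or analysis plan, which is not shown.

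Much of this stands. It rules out some stronger readings that a reader might infer:

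- *That people who stop a supplement vanish from that supplement's own result.* On the adherence check described, T2 or T4 would usually have been recorded by the time packages are returned. The main loss is the later period, under the other supplement.
- *That the analysis is per-protocol in effect.* A per-protocol analysis would drop the data of all non-adherers. Here exclusion is discretionary and available data are kept.
- *That a definite bias follows.* If 15% were removed under one supplement only, each 10 points worse than the rest, that supplement's mean would rise by 0.15 × 10 = 1.5 points. No section supports any of those inputs.
- *That the threshold works differently for sachets and bran.* An empty bran pack is a weaker record of daily intake than counted sachets, but the article does not say how the bran is packed, and section 4 already concedes that strict control of adherence is impossible.

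What the reply does not answer is conduct. The exclusion rule is stated here, it is discretionary and unblinded, and nothing here keeps those excluded in follow-up. An analysis plan can define sets; it cannot supply assessments that were not made.

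**Conclusion.** The point holds as an unreconciled conflict between the exclusion rule in section 2.2 and the intention-to-treat commitment in section 3. Followed as written, the rule can cause selective, discretionary loss of outcomes: chiefly T3 and T4 after exclusion at the end of period 1, and possibly every post-baseline GIQLI after exclusion during period 1.

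The direction and size of any bias cannot be determined from the article. The loss of precision is modest for a few exclusions and noticeable for many: about 83%, 81% and 76% power with 3, 5 and 10 lost, against the stated 85%. Those figures rest on a back-solved SD, a two-sided paired comparison, assumed numbers lost and no contribution from incomplete participants. Any dropout would cost power in the same way. What is particular to this rule is that trial staff cause the loss and could avoid it.

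**What to change.** Reconcile sections 2.2 and 3 by stating that:

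1. Non-adherence, or stopping a supplement, does not end outcome collection. The remaining GIQLI assessments are sought from every randomised participant who has not withdrawn consent.
2. All available post-baseline GIQLI values enter the primary mixed model under the randomised sequence, whatever the intake.
3. The 25% threshold serves only to define a supplementary per-protocol set, by a fixed rule written before the analysis and with no case-by-case discretion. The rule should say whether the threshold applies per period or overall. Because the trial is open-label, the safeguard is the fixed rule and its date, not concealment of the supplement.

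This concerns outcome collection and analysis only; it takes no position on whether a participant should go on taking a supplement.

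The cost is a minor amendment and some effort to retain participants who have stopped. The estimate may be slightly diluted by non-adherence, which comes with an intention-to-treat question. Recruitment began in summer 2025 and the study is expected to end in summer 2027, so the change is worth making soon: assessments missed in the meantime cannot be recovered.

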### 2.3. Intervention

The probiotic intervention involves an 8-week supplementation with the commercially available probiotic BIOTICS-G (Burgerstein AG, Rapperswil-Jona, Switzerland). Participants take one sachet (2.5 g) daily, mixed into 50–100 mL of water 30 min before breakfast or dinner. Biotics-G supplies fourteen lactobacilli and bifidobacteria strains together with Saccharomyces boulardii, delivering 2.5 × 10^9^ CFU per sachet. The composition closely mirrors Bactosan^®^ Pro-FOS, which improved microbial diversity and reduced systemic inflammation in a crossover pilot study involving wheelchair athletes with spinal cord lesions [35]. Bactosan^®^ Pro-FOS is no longer on the Swiss market, which is why the alternative probiotic BIOTICS-G had to be chosen. The present trial extends that evidence to a community cohort.

The prebiotic intervention involves taking a prebiotic supplement for 8 weeks. The participants take 5 g of oat bran daily (Oat Bran, Naturaplan, manufactured by Swissmill, Zurich, Switzerland), mixed in with their usual breakfast or dinner.

The probiotic supplementation serves as the intervention of interest and the prebiotic supplementation as an active comparator, based on the literature and a pilot study [35,43].

Participants are instructed to maintain their usual training routine and diet, to minimize the chance of potential health modifications to be attributable to any factor other than the intervention with pre- or probiotics. Participants receive weekly reminders to take supplements and are asked to return empty packages to the study center after the intervention periods as a means of control of adherence to supplementation.

The first intervention phase is followed by a 4-week washout period to prevent carryover effects. Previous studies in non-disabled individuals have proven 1–2 weeks to be sufficient for effects of inulin-type fructans (prebiotics) to disappear after the intake has ceased [44]. To ensure adequate washout in our study population, the washout period is extended to four weeks.

### 2.4. Assessments

Outcome data are gathered at four timepoints: baseline (T1), after the first eight-week intervention phase (T2), after the four-week washout (T3), and after the second intervention phase (T4) - an overview can be found in Table 1. The primary endpoint is the GIQLI, indicating changes in subjective GI health [45]. The GIQLI is a questionnaire consisting of 36 questions assessing health-related quality of life in GI disorders, each on a scale from 0 to 4 [46]. It captures a person’s own perception of symptoms, functional limitations, and the psychosocial impact thereof. The GIQLI can range from a score of 0 to 144, with higher scores indicating better gut health and satisfaction with gut health.

Secondary endpoints cover gastrointestinal transit, systemic and mucosal biology, and safety. GITT is measured in the home setting with the Blue Dye Method, defined as the interval between ingestion of blue food coloring on an empty stomach and the first and last appearance of blue-colored stool [47,48]. Blood serum collected at each visit is analyzed with the Olink Target 48 Cytokine panel (Olink Proteomics AB, Uppsala, Sweden), which quantifies 45 inflammation-related proteins, including cytokines and chemokines such as IL-2 and TNF-α. These markers have been shown to be elevated in the serum of individuals with chronic SCI patients compared to healthy controls [49]. Fecal microbial community structure is characterized by full-length 16S rRNA gene sequencing on the MinION Nanopore sequencer (Oxford Nanopore Technologies, Oxford, UK). DNA is extracted with the QIAamp PowerFecal Pro DNA kit (QIAGEN, Hilden, Germany) using ten-minute bead-beating with 0.1 mm zirconia beads, quantified with Qubit™ 4.0 dsDNA HS fluorimeter (Thermo Fisher Scientific, Waltham, MA, USA), and prepared with the MinION Nanopore Ligation Sequencing Kit (SQK-LSK114) plus native barcodes (EXP-PBC096) (Oxford Nanopore Technologies, Oxford, UK). Libraries are pooled equimolarly, loaded on R10.4.1 flow cells, and base-called with Dorado; reads below a quality score of 9 are discarded. Emu assigns taxonomy. Supplement tolerance and all adverse events are documented throughout the study.

Variables that may influence these outcomes are captured systematically. At T1, each participant provides age, sex, lesion level and completeness, time since injury, body mass, and current medication (Appendix, Table A1) Physical activity is quantified with the Leisure-Time Physical Activity Questionnaire for persons with SCI (LTPAQ-SCI) [50], while autonomic function is evaluated with the ISAFSCI (second edition, 2021) tool [51]. Dietary intake is recorded with a three-day diary before every visit and processed in Prodi 7.4 (Version 7.4, Nutriscience, Stuttgart, Germany); mean energy, fiber, saturated fat and alcohol intakes are used in sensitivity analyses to mitigate dietary confounding.

Sample logistics follow a standardized pipeline. During the week preceding each visit, participants collect stool in the OMNIgene^®^ GUT (DNA Genotek, Ottawa ON, Canada) and draw 4.9 mL of venous blood into an S-Monovette Serum tube (Sarstedt, Sevelen, Switzerland). Blood is centrifuged within thirty minutes at 1800× *g*, 20 °C, for fifteen minutes. Plasma is aliquoted in 500 µL volumes and stored at −80 °C. Stool is vortexed on arrival, subdivided into 250 µL aliquots, and frozen at −80 °C. To align sampling with supplementation phases, T1 occurs one week before tablets or oat bran are first taken, providing sufficient time to complete home procedures. Thereafter, all home collections take place in the week before each center visit, so that the full protocol spans 21 weeks although active supplementation occupies 20 weeks. Participants receive weekly electronic reminders covering supplement intake, as well as the timing of stool, diary, and GITT procedures.

## 3. Data Analyses

An intention-to-treat analysis will be conducted to minimize potential bias resulting from disruption to baseline equivalence following randomization, which may occur due to participant withdrawal, non-adherence to the study protocol, or excessive missing data. Participants will be included in analyses only where data are available. Protocol deviations, early withdrawals, and loss to follow-up will be documented and evaluated. Basic univariable statistical analysis techniques will be used to describe the study population as well as the primary and secondary outcomes at the different measurement points. To evaluate the longitudinal variation in the primary outcome and secondary outcomes, we will use multilevel mixed-effects models that appropriately account for the within- and between-individual sources of variance in outcome variation. In these models, participants are treated as random effects, while intervention and period are used as fixed effects. All models will be adjusted for the baseline value of the respective outcome measured before each period. To evaluate potential carryover effects, sequence (AB vs. BA) will be included as a fixed effect, and treatment-by-period interactions will be tested. Furthermore, pre-period baselines will be compared to verify that the gut environment returned to its SCI-baseline during washout, and a carryover term will be incorporated into the model to identify residual effects. If significant carryover is detected, a sensitivity analysis using only period 1 data will be performed to provide an unbiased estimate of the intervention effect. Depending on the findings, subgroup analyses may be performed for personal parameters (e.g., sex, lesion level). For the microbiome analyses, diversity indices will be compared using paired *t*-tests while correcting for multiple testing using the Benjamini–Hochberg method. A significance level of 5% will be applied. Protein concentrations will be reported as absolute abundances in pg/mL. Absolute abundance will be tested with mixed-effects models analogous to the primary analysis. The Benjamini–Hochberg procedure will control the false-discovery rate at 5%. Multi-omics integration will employ sparse partial least-squares regression to relate inflammatory proteins, microbial genera, and clinical outcomes (GIQLI, GITT). Statistical software packages to be used include R (Version 4.5.2), Stata (Version 19.0), and SPSS (Version 31.0), or any newer stable version available at the time of data analysis.

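### A single slope for the period-specific baseline mixes between- and within-person associations and costs the crossover treatment estimate precision; splitting the baseline is a cheap improvement

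*Protocol article*

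**What the plan says.** In section 3 of the protocol article, the mixed models for the primary and secondary outcomes are set up so that "participants are treated as random effects, while intervention and period are used as fixed effects". Sequence is added as a further fixed effect. On baseline the text says: "All models will be adjusted for the baseline value of the respective outcome measured before each period". Period 1 therefore takes T1 and period 2 takes T3. One adjustment is named, and no division into a person-level part and a within-person part is mentioned. The protein models are to be analogous to the primary analysis.

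Section 2.1 gives the sizing: "The sample size was calculated for the primary outcome (changes in GIQLI) based on the results of a previous pilot study", "applying a clinically relevant mean difference of 10 points on the GIQLI" and "correcting for a larger expected variability in the GIQLI in the current study population". It continues: "Assuming a significance level of 5% and a power of 85%, a sample size of 50 participants, with 25 participants in each group, was determined". It states no SD, no within-person correlation and no estimator.

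**The concern.** Each participant receives both supplements, so the treatment effect is estimated from the difference between that participant's two outcomes, T2 and T4. The only baseline information that can sharpen this contrast is the difference T1-T3, and its proper weight is the within-person slope: how far T2-T4 moves when T1-T3 moves.

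A single time-varying baseline in a random-intercept model has one slope for two relations. People with high baselines have high outcomes, and this between-person relation is usually strong. The within-person relation may be weak or absent. REML averages the two, and the average is then applied to T1-T3. If T1-T3 is mostly noise, the adjustment adds noise to the treatment estimate. Section 4 of the article justifies the crossover by its higher power, and this form of adjustment can give part of that back in the GIQLI, transit-time and protein models.

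**Working it through.** **1. Inputs.** From section 2.1: 10 GIQLI points, 5% level (two-sided assumed), 85% power, N = 50, 25 per sequence. From section 3: the model above. Correlations among T1 to T4 are assumptions, because the article gives none. Equal variances are also assumed.

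**2. The plan's own figure.** N = 50 cannot be reproduced, only back-solved. With z = 1.960 + 1.036 = 2.996:
- Paired comparison, n = 50: SD of the within-person difference = 10 × √50 / 2.996 = 23.6 points.
- Two-sample comparison, 25 against 25: SD = 10 × √(25/2) / 2.996 = 11.8 points.

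**3. Variance of the treatment estimate.** Let D = T2-T4 and X = T1-T3, with slope b applied to X. The estimate is half the difference between sequences in the mean of D - bX, so its variance is Var(D - bX)/50. With Var(X) = Var(D) and within-person slope w = Cov(D, X)/Var(X):
- relative to no baseline: 1 - 2bw + b²
- relative to a split baseline: (1 - 2bw + b²) / (1 - w²)

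**4. Equal correlation r.** Here w = 0 and the between-person slope is 2r/(1 + r). The fitted b and the power come from simulating random-intercept REML models with treatment, period, sequence and baseline (N = 50, 6,000 replicates per scenario; the fit agreed with a standard mixed-model routine on 12 data sets). Power is calibrated so that the unadjusted within-person difference has 85%.

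| r | Between slope | Within slope | Fitted b | 1 + b² | Power, single | Power, split |
|---|---|---|---|---|---|---|
| 0.5 | 0.67 | 0 | 0.44 | 1.19 | 79% | 84-85% |
| 0.6 | 0.75 | 0 | 0.54 | 1.29 | 74% | 84-85% |
| 0.7 | 0.82 | 0 | 0.65 | 1.42 | 72% | 84-85% |
| 0.8 | 0.89 | 0 | 0.77 | 1.59 | 66% | 84-85% |

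The simulated standard errors agree: 3.58 against 3.30 at r = 0.5 (ratio squared 1.18) and 3.89 against 3.31 at r = 0.7 (1.38). At r = 0.2 the factor is only 1.03. With correlations that decay over weeks 0, 8, 12 and 20, power is 75-81% against 84-86% split.

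**5. Baseline closer to its own period's outcome.** With own-period correlation p and all other correlations q, w = (p - q)/(1 - q). Power is calibrated as in step 4.

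| p / q | w | Fitted b | Variance vs none | Variance vs split | Power, single |
|---|---|---|---|---|---|
| 0.6 / 0.5 | 0.20 | 0.56 | 1.09 | 1.13 | 82% |
| 0.8 / 0.7 | 0.33 | 0.78 | 1.09 | 1.22 | 83% |
| 0.7 / 0.5 | 0.40 | 0.68 | 0.92 | 1.09 | 89% |
| 0.8 / 0.5 | 0.60 | 0.79 | 0.68 | 1.06 | 96% |
| 0.6 / 0.3 | 0.43 | 0.58 | 0.84 | 1.03 | 90% |

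The written model beats no adjustment when b < 2w, as in the last three rows. At 0.7 / 0.5 the loss against the split is √1.09, about 4-5% in standard error (3% in simulation: 2.882 against 2.786). At 0.6 / 0.3 the two are practically equal in simulation (2.831 against 2.816).

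**6. Power against 85%.** Power is about Φ(2.996/√k - 1.960), where k is the variance relative to the one used for planning. Take equal correlation 0.7:
- N = 50 planned on the unadjusted difference: k = 1.42, power about 71% (simulated 72%).
- N = 50 planned on change scores (slope 1, factor 1 + 1² = 2): k = 1.42/2 = 0.71, power about 94% (simulated 95%).

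Over all structures tried, change-score planning gives 89-99%. Planning on the unadjusted difference goes as low as 62% (r = 0.9). Under the two-sample reading (SD 11.8 per measurement), the simple crossover comparison already has about 99% or more.

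**7. Bias.** Without carryover the mean estimate is 9.9 to 10.1 for a true 10, and type I error is 5.0% and 4.7% (r = 0.5 and 0.7). Now let one treatment leave a residue δ at T3 and λ at T4, in SD units. Under equal correlation the bias is ½(bδ - λ) for the single slope and -λ/2 for the split. With b = 0.65 and δ = 0.25:

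| λ at T4 | Single: bias (type I error) | Split: bias (type I error) |
|---|---|---|
| 0 | +0.08 (9%) | 0 (5%) |
| 0.125 | +0.02 (4%) | -0.06 (8%) |
| 0.25 | -0.04 (6%) | -0.13 (19%) |

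**The case against.** A reader might infer three stronger claims. None is supported.

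- *Power falls below the stated 85%.* Section 2.1 sizes the trial for changes in GIQLI without an SD, correlation or estimator. If the change-score variance was used, step 6 puts the written model above 85% in every structure tried. The shortfall appears only if N = 50 rests on the unadjusted within-person difference and a baseline is little closer to its own period's outcome than to the other's.
- *The adjustment is worse than none.* Step 5 shows the reverse for plausible correlations. Nothing is known about the correlations of GIQLI, transit time or 45 proteins, so no general statement is possible.
- *T3 follows randomised treatment, so the written model is biased and the split cures it.* Step 7 shows that this holds only if the residue at T3 has gone by T4. If it persists to T4, the split is the more biased. Section 3 also already plans a comparison of pre-period baselines, interaction and carryover terms, and a period-1 sensitivity analysis.

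It is also fair to say that covariate coding is often left to an analysis plan. None is shown here, and the article does not exclude a split. These objections remove the claims about power and bias. They do not remove the precision point: the article states a concrete adjustment, and in no structure tried did the split do materially worse.

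**Conclusion.** The point holds as a matter of precision. Read as written, the adjustment gives a treatment estimate less precise than the same data allow. The excess variance over a split baseline is about 20-60% for assumed equal correlations of 0.5 to 0.8. It shrinks to a few percent in standard error when a baseline is clearly closer to its own period's outcome. The figures rest on assumed correlations, equal variances and complete data. The documents settle neither the direction of power against 85% nor any advantage in bias. The analysis is valid without carryover, so this is a cheap improvement, not a flaw that must be repaired before the trial can be interpreted.

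**What to change.** For GIQLI, transit time and the proteins, replace the single baseline covariate with two: the participant's mean of T1 and T3, and each period's deviation from that mean. With both periods complete, this is equivalent for the treatment effect to regressing T2-T4 on T1-T3 with sequence as a factor.

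The cost is one sentence and one degree of freedom, about 1-3% in variance if the baseline difference carries no information. The mean needs both T1 and T3, so the sentence should also say how participants who leave before T3 are handled; they add little to the within-person contrast. The split gives no protection against carryover that persists to T4, so the planned carryover checks remain necessary.
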